### 5.3 Auditing

By signing the protocol, the investigator agrees that the sponsor, its representative and regulatory agencies have direct access to its study records for the purpose of an audit or an inspection. These personnel, bound by professional secrecy, will not divulge any personal identity or any personal medical information. In all cases, the sponsor will assist the investigator in preparing for an inspection by a regulatory authority.

## 6 Ethics and dissemination

### 6.1 Research ethics approval

This trial involving human participants has been reviewed and approved by ethics committee on 14 November 2022 (CPP IDF VII 2022-A1967-36). The study and has been registered on ClinicalTrial.gov (trial registration number NCT05661383) before its completion on 12 December 2022.

### 6.2 Consent

The study will be conducted in accordance with the Declaration of Helsinki.

Before consent is obtained, each patient will receive an information notice explaining, in comprehensible terms, the purpose of the study, the course of the study, associated risks and benefits, as well as their right to refuse to participate in the study and to withdraw at any time. An inclusion visit will be then scheduled, during which the investigator will reiterate this information and answer any questions the participant may have. Only after ensuring complete understanding, written informed consent will be obtained from a psychiatrist involved in the study. Both parties will sign copies of the consent form, with one copy given to the participant and the other kept by the investigator.

### 6.3 Confidentiality

All participant-related information will be collected in a paper CRF and reported in an electronic database. The data flow has been declared and approved by the CNIL (National Data Privacy Commission). To ensure confidentiality, all participant documents will be anonymized and will display only an ID code consisting of the treatment group number, serial number and patient initials.

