## 3 Methods: assignment of intervention

### 3.1 Sequence generation

Patients will be randomly assigned (1:1) to receive either iTBS alone or iTBS combined with pleasant olfactory stimulation. Computer-generated random numbers using the Sealed Envelope platform (https://www.sealedenvelope.com) will be used to generate the allocation sequence. Block of 2, 4, and 6 will be used to stratified the randomization.

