### 3.2 Allocation concealment mechanism

The allocation sequence will be handled by an independent person from the Administrative Department of the Hospital to ensure that it is not disclosed to those responsible for enrolling and allocating patients.

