### 3.3 Implementation

All the included participants will be assigned to a unique anonymous identification code, consisting of the group assignment number, the inclusion number and the patient's initials (first letter of last name and first letter of the first name). The person providing care will then administer the appropriate treatment associated with the inclusion number, according to the order of assignment.

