### 3.4 Blinding

To ensure that patients are blinded to the allocated treatment, the information notice distributed to patients will state that odorants will be diffused during the TMS sessions, but at either a supraliminal or subliminal concentration, meaning that it may be normal not to smell anything. In addition, both the clinicians who complete the clinical scales and the researchers who analyze the data will be blinded to the allocation.

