### 4.4 Statistical methods

#### 4.4.1 Statistical methods for analyzing primary and secondary outcomes

Statistical analysis will be performed using R studio (Boston, USA, with the latest version at the time of the analysis) by an experimenter blinded to treatment allocation. The alpha threshold will be fixed at 0.05. Parametric tests will be performed only when the assumptions for their application are met, otherwise, non-parametric tests will be performed.

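### The participant ID code contains the treatment group number, which conflicts with the stated blinding of raters and analysts

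*Protocol article*

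**What the plan says.** Two sections of the protocol article define the identification code. Section 3.3 (Implementation) describes it as "consisting of the group assignment number, the inclusion number and the patient's initials". Section 6.3 (Confidentiality) says that participant documents "will display only an ID code consisting of the treatment group number, serial number and patient initials". On which records are meant, Section 6.3 adds: "All participant-related information will be collected in a paper CRF and reported in an electronic database".

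Other sections promise blinding and concealment. Section 3.4 says that "both the clinicians who complete the clinical scales and the researchers who analyze the data will be blinded to the allocation". Section 4.4.1 has the analysis done "by an experimenter blinded to treatment allocation". Section 6.6 keeps the double blind through the 3-month follow-up. Section 3.2 gives the sequence to an independent administrator "to ensure that it is not disclosed to those responsible for enrolling and allocating patients". Section 3.1 publishes the block sizes: "Block of 2, 4, and 6 will be used to stratified the randomization".

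**The concern.** An identifier that appears on every participant document should carry no information about allocation. Here its first element is a group number, and Section 6.3 calls it the treatment group number.

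The primary endpoint is remission on the MADRS (Section 2.4.1), and Section 4.2.1.1 describes that scale as clinician-rated. Section 9 concedes that keeping patients unaware of their group is a major limitation, because one group is exposed to odorants and the other is not. Rater blinding therefore carries much of the protection against biased ratings, and the code undermines it on the page where the rating is recorded. If a rater's expectation did influence scores near the remission cut-off, no later analysis could reliably remove that influence.

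**Working it through.** The plan gives no figure on this point. The main check sets the sections against each other; a small calculation follows for allocation concealment.

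**1. Is the group number a slip of wording?** Sections 3.3 and 6.3 define the code separately, and both start it with a group element. A single slip is unlikely.

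**2. Would a rater see it?** Section 6.3 applies the code to all participant documents and says participant information is collected in a paper CRF. Section 4.3 confirms that clinical data go into a CRF. Table 1 places allocation at week 0 and the post-treatment MADRS at week 2, so the number exists by the time the primary endpoint is rated. That the rater works on a page bearing the code is an inference, but it is the natural reading of all participant documents.

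**3. Does any section mask the number?** None does. Section 6.5 gives those analysing the data an anonymized data set, and Section 6.3 describes anonymized documents as the ones carrying this code. Section 7.3 states that the article is the full protocol.

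**4. What follows for raters?**
- Meaning of the number known: the rater reads the arm from the page.
- Meaning not known (a neutral 1 or 2): the rater sees two labelled sets of patients. What one patient reveals about perceiving an odour then bears on every patient with the same label, up to all 80. With an allocation-neutral code it would bear on that patient only.

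**5. What follows for the analyst?** Comparing two arms needs an arm label, and a neutral 1 or 2 is compatible with a blinded analysis. Analyst blinding fails only if the meaning of the number is known.

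**6. What follows for concealment?** Suppose recruiters see all earlier codes, know what the number means, and always guess the arm that is behind (a coin toss when level). For a block of size 2m, the expected number of correct guesses is m + ½·(4^m / C(2m, m) − 1):

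| Block size | Expected correct | Rate |
|---|---|---|
| 2 | 1 + ½(4/2 − 1) = 1.50 | 75.0% |
| 4 | 2 + ½(16/6 − 1) = 2.83 | 70.8% |
| 6 | 3 + ½(64/20 − 1) = 4.10 | 68.3% |

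With the three sizes equally likely (an assumption; Section 3.1 does not say), the rate is (1.50 + 2.83 + 4.10) / (2 + 4 + 6) = 8.43/12 = 70.3%. A simulation of 20,000 sequences of 80 patients gives 70.2%. Full concealment gives 50%. Other mixes of these sizes stay between 68.3% and 75.0%.

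Allocations fixed by a running imbalance of 3 are rare. They need a block of 6 that opens with three alike, which has probability 2/20 = 0.1. That gives 0.1/12 = 0.8% of allocations, and the simulation also gives 0.8%.

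**The case against.** The strongest reply is that the article never says what the number stands for. Section 3.3 gives the code to all included participants, and the study also enrols 40 healthy volunteers, so the group could be patient versus volunteer. Section 3.3 also links treatment to the inclusion number, and inclusion (week −1) precedes allocation (week 0) in Table 1, so inclusion documents could not at first have carried an arm number. This reading is possible for Section 3.3 alone. It fits poorly with Section 6.3, which says treatment group number.

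A reader might infer that blinding is certainly broken, or that one patient mentioning a smell decodes all 80. The documents do not support either. A neutral number discloses nothing by itself. Sections 3.4 and 9 say patients are told that odorants may be above or below the threshold of perception, and Section 9 adds that patients are asked not to share their feelings about the treatment, to protect evaluators. A reported smell is therefore suggestive, not decisive. What stands is that a shared label turns a leak about one patient into information about many.

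A reader might also take the 70% as the measured effect of the ID rule. It is not. It requires recruiters to see every earlier code and to know its meaning; with a neutral code they would predict the next number, not the next treatment. The sequence itself stays with the independent person of Section 3.2. Section 3.1 also uses the word stratified without naming a factor, and a factor would change the figure.

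**Conclusion.** The contradiction is real and the rule is wrong as written. Sections 3.3 and 6.3 put a treatment group number on all participant documents, while Sections 3.4, 4.4.1 and 6.6 promise blinded raters, a blinded analyst and a lasting double blind, and nothing in the article reconciles them.

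Its reach is every post-allocation rating of all 80 planned patients, including the primary MADRS rating. Its severity depends on a fact that the article does not give:
- If the number's meaning is known, the rater sees the arm.
- If it is neutral, blinding is weakened and not lost, through the link between patients who share a label.
- The analyst's blinding is at risk only in the first case.
- The effect on allocation concealment is indirect and conditional: about 70% correct guesses against 50%, under the assumptions in the working.

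The documents do not allow an estimate of how far MADRS ratings or the remission comparison would be biased, and none is claimed.

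**What to change.** Amend Sections 3.3 and 6.3 so that the ID code has no group element and identifies the patient by serial or inclusion number. Nothing operational is lost, because Section 3.3 already ties treatment to the inclusion number. Keep the code-to-arm key only with the independent person of Section 3.2 and the treatment operator. Give the analyst a separate dummy arm label that does not appear on participant documents, which keeps the blinded analysis of Section 4.4.1 workable. Relabel the documents of patients already included.

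If the group element was meant only to separate patients from healthy volunteers, the amendment should say so in words that cannot be read as treatment arm.

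The cost is relabelling existing documents and a short amendment. Sample size, endpoint and analysis are unaffected.

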### 6.5 Access to data

The study sponsor will have full access to the final data set at the end of the trial. Anonymized data will be made available to those responsible for statistical analysis and may be shared with other researchers upon reasonable request and in accordance with EU regulation - GDPR.

### 6.6 Ancillary and post-trial care

Patients will remain under double-blind throughout the follow-up period with no change in treatment. Follow-up will be carried out for a period of 3 months. After inclusion, patients may not participate in any other clinical research will be permitted during the study.

## 7 Dissemination policy

### 7.1 Communication of trial results

Results will be presented at national and international scientific meetings and conferences. Articles will be submitted to international peer-reviewed journals. Anonymized dataset may be shared with other scientists upon reasonable request. The sponsor of the study and the funders play no role in the design of the study, no role during its execution, analyses, interpretation of the data, or decision to publish the results.

### 7.3 Plans to give access to the full protocol, participant level-data and statistical code

This manuscript is the full protocol of the study. Anonymized dataset and statistical code may be shared with other scientists upon reasonable request.

## 8 Discussion

Thirty percent of individuals suffering from MDD are resistant to pharmacological treatments, underscoring the urgent need for novel therapeutic alternatives to treat depression. rTMS has been proposed as an innovative tool to alleviate depressive symptoms. Although approved by health authorities in certain countries for the treatment of major depression, the considerable heterogeneity in clinical response leaves much room for optimizing its application in clinical settings. Here, we propose the first randomized, double-blind, controlled trial to investigate clinical and biological effects of the combination of hedonic olfactory and brain stimulations.

The iTBS protocol proposed in this study seems to be appropriate, considering that other studies have already shown its efficacy on depressive symptoms (Duprat et al., 2016; Cole et al., 2022; Wilkening et al., 2022), its safety across numerous psychiatric condition (Caulfield et al., 2022; Brunelin et al., 2022) and that accelerated protocols allows a better access to treatment for patients (Mondino et al., 2021). The use of pleasant odorants to modulate neural activity within the reward system is grounded in the close connection between this system and the olfactory one, through structures like the olfactory tubercle. Moreover, stimulation of the left DLPFC is thought to result in the release of subcortical DA (Fonteneau et al., 2018; Brunelin et al., 2011; Strafella et al., 2001), which may help stimulate the reward circuitry.

The knowledge gained from in this project will strengthen the development of more effective NIBS strategy and pave the way for the establishment of NIBS combined with olfactory training as a safe, effective, and easily accessible treatment for patients with both unipolar and bipolar major depressive episode.

In addition, anhedonia can also be considered as a transdiagnostic symptom that is common to psychiatric disorders, including schizophrenia and post-traumatic stress disorder. From this perspective, a similar protocol could potentially be applied to address this symptom across a range of psychiatric conditions.

Finally, this study will provide a better understanding of the mechanisms and pathophysiology of major depressive episodes and depressive symptoms (especially anhedonia), as well as the mechanisms of action of rTMS. Dual-coil TMS, iTBS protocol and fMRI will allow us to better understand the role of the DLPFC in anhedonia.

## 9 Limitation

Ensuring that participants are blind to their assigned group is a major limitation. To limit this bias, participants are informed that the odorants may be at a supraliminal or infraliminal concentration, which could explain the difference in perception. This approach ensures that the participant believes in the presence of an odorant. To maintain the evaluators' blindness, participants are asked not to share their feelings about the treatment.

Finally, we are constantly in an environment rich in sensory stimuli, and the design of this study does not allow us to control for patients' previous exposure to odorants or other forms of sensory stimuli. However, the verification of the absence of anosmia, the fixed list of odorants presented, the selection of the three most appreciated odorants, and the time-limited exposure to odorants during the iTBS sessions provide a clear methodological control for this study.

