### 5.2 Harms

Safety assessment will be conducted in accordance with French law. Adverse events attributable to treatment will be verified, assessed and categorized by the principal investigator in the appropriate section of the CRF. This includes any adverse events observed by the investigator as well as any adverse events reported by the participant.

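### The instruction that protects rater blinding is worded broadly enough that it may discourage patients from reporting adverse events

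*Protocol article*

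**What the plan says.** Three parts of the protocol article meet here.

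- **Blinding (sections 3.4 and 9).** Patients are told that "odorants will be diffused during the TMS sessions, but at either a supraliminal or subliminal concentration", so that smelling nothing seems normal. On the assessors' side, "both the clinicians who complete the clinical scales and the researchers who analyze the data will be blinded to the allocation". Section 9 calls patient blinding a major limitation and adds that, to keep the evaluators blind, "participants are asked not to share their feelings about the treatment".
- **Harms (section 5.2).** "Adverse events attributable to treatment will be verified, assessed and categorized by the principal investigator in the appropriate section of the CRF". On sources: "This includes any adverse events observed by the investigator as well as any adverse events reported by the participant".
- **Roles (sections 3.3 and 4.1.1).** Clinician-rated scales are scored by psychiatrists. Treatment is given by someone else or by an unspecified member of staff: "The person providing care will then administer the appropriate treatment associated with the inclusion number, according to the order of assignment". This role is not in section 3.4's list of blinded persons.

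Table 1 has no row for adverse events. Section 7.3 states: "This manuscript is the full protocol of the study".

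**The concern.** Section 5.2 needs patients to speak about what the treatment does to them. Section 9 asks the same patients not to share how they feel about it. A patient hears the instruction, not the reason for it. Headache, nausea, agitation or dislike of the odour could each be taken as a feeling about the treatment and kept back, above all in front of a psychiatrist.

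Two things are at stake. The abstract and section 8 hope that the work will help establish the combination as a safe treatment, and a low count of reported events is hard to interpret if patients were discouraged from reporting. Also, a tolerability problem during a course of 50 sessions in two weeks might reach the investigator late or not at all.

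**Working it through.** The plan states no figure on this point, so there is none to reproduce. The check compares the texts.

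1. **Scope of the instruction.** Its purpose is stated (evaluator blinding), but its content is wider than that purpose. Evaluator blinding needs silence on two matters only: whether an odour was perceived, and which group the patient believes they are in. Section 9 restricts feelings about the treatment in general. It names no recipient, lists no exception and gives no end date. Section 6.6 keeps the double blind through the three months of follow-up.

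2. **What harms capture depends on.** Section 5.2 names two sources, observation and participant report. Subjective complaints can reach the record only through the second. Section 5.2 also concerns events attributable to treatment, and attribution often rests on the patient linking a complaint to the sessions. That is the kind of remark the instruction can discourage.

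3. **Who hears the report.** The principal investigator verifies and categorises events. The article does not say who asks for them, or whether that person also rates the MADRS. If a rater asks, the two rules collide in the same conversation. If someone else asks, they need not collide, but the patient has not been told so.

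4. **Whether the schedule compensates.** Table 1 shows no adverse-event assessment at any visit. The YMRS, listed in section 2.4.2 for manic states, has no row either. So the schedule shows no structured enquiry that would make up for lost spontaneous reports.

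5. **Whether the arms differ.** The instruction is the same in both arms, and the information notice tells patients that odorants will be diffused. Let q be the true event rate and w the share withheld, with subscripts C (combined) and A (iTBS alone).
 - Observed rate in each arm: q × (1 − w).
 - Observed ratio: (q_C / q_A) × (1 − w_C) / (1 − w_A).
 - If w_C = w_A, the ratio is unchanged and both rates are too low by the same factor.
 - The ratio falls only if w_C > w_A. The article offers one route to that: only the combined arm receives an odorant (section 2.3), so complaints about a perceived odour would arise mainly there. Ordinary complaints about iTBS are common to both arms.

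6. **Size.** Neither q nor w is given for either arm. With w = 0, which the document does not rule out, nothing is lost. No numerical estimate is justified.

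**The case against.** The strongest reply is that the two sections can be read together without conflict. The instruction's declared aim is the evaluators' blinding, so its natural meaning is that patients should not give raters their impressions of the treatment. A symptom is not a feeling about the treatment on the ordinary reading. Section 5.2 is the specific provision on harms, and it expressly accepts participant reports. Nothing tells patients to conceal an adverse event, and nothing stops them from telling the staff who run the sessions. The information notice, which may be worded more carefully, is not shown. This reply stands as far as it goes: there is an unresolved ambiguity, not a prohibition.

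A reader might infer three stronger things, and the documents support none of them:

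- *That the rule suppresses reports.* No passage says so, and section 5.2 points the other way.
- *That the loss falls mainly on the combined arm.* The instruction is common to both arms. A difference is conceivable only for odour-specific complaints, and the odorants diffused come from each patient's three highest-rated ones (section 2.3).
- *That the rule bars a separate reporting route.* It bars none; the article simply does not describe one.

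The reply does not remove the point altogether. The broad wording is something the article states, not a detail left out in condensing, and section 7.3 presents the article as the full protocol.

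**Conclusion.** The concern holds as a wording problem that is worth a cheap correction. The instruction is wider than its purpose needs, harms capture depends on patients speaking, and the harms collector is not separated from the blinded raters. As worded, it may discourage adverse-event reports in both arms, and possibly more so for odour-related complaints in the combined arm.

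The size is unknown and may be zero. The conclusion assumes that at least some patients would take the instruction literally and that the notice adds no exemption for symptoms. It does not affect the primary remission analysis. It bears on how far a low adverse-event count could be taken as evidence of safety.

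**What to change.** - **Reword the instruction in the protocol and the information notice.** Patients should not tell the clinician who rates them whether they smelled an odour or which group they think they are in. They should report any symptom or discomfort at any time.
- **Separate the roles.** Existing staff who do not rate the MADRS take these reports, ask the same question in both arms, and record the answers on a CRF page that the rater does not see.

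This serves harms capture, and it also protects rater blinding better, because it tells patients exactly what to keep from the rater.

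**Cost:** a small rewording, one CRF page and a little staff time. **Downside:** if the person who collects reports knows the allocation, that knowledge may colour how events are elicited or recorded. Asking the identical question in both arms limits this but does not remove it. Fixed questioning after each treatment day or at each follow-up visit is optional and not needed to resolve the point.
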